### Ethics and data security

Physicians participating in the peer CME groups will be given information about the objectives of the study and the practical impact it may have on their practice. They will be told that each peer CME group will be randomized to one out of two interventions (improved antibiotic prescriptions for RTIs or improved prescription patterns in elderly ≥ 70 years), and that they will serve as control group for the intervention they do not take part in. Participation is based on written informed consent from all physicians. The project has been presented for The Regional Committee for Research Ethics and approval from The Norwegian Social Science Data Services (NSD) has been obtained, implicating acceptance to extract prescription data. In order to use patient identification data in the merging process between NorPD and EPR databases, The Directorate for Health and Social Affairs has approved dispensation from the health-professional secrecy.

### Sample size and statistics

A prevalence of 27% of inappropriate prescriptions of antibiotics for RTIs in general practice settings were found in two previous studies; one from Norway [80] and one from The Netherlands [62]. In accordance with these findings [62,80], we anticipate a baseline prevalence of inappropriate prescription of antibiotics for RTIs of 27% in the present study.

Flottorp et al. [63] demonstrated a 3% reduction of inappropriate antibiotic prescription for sore throat in a tailored intervention in general practice settings. This intervention was not, however, based on peer CME groups. This was considerably less than the 12% reduction (absolute value) of antibiotic prescription rates for RTIs found by Welschen et al. [62], in a peer group intervention trial.

In the present study we will consider a reduction of inappropriate prescriptions for RTIs by one third to be clinically significant. Assuming that the prevalence of inappropriate prescriptions in the control group remains constant, this equals a reduction from a baseline level of 27% to a post-intervention level of 18% or less (9% absolute reduction; 33% relative reduction).

The sample size calculation needs to take into account and adjust for intra-cluster (peer group) correlation, since the data within peer groups cannot be considered independent. The intra-cluster correlation is assumed to be 0.085, based on data from previous studies [63,78]. Furthermore, we expect an average of 7 participating doctors per peer group (allowing for some withdrawal) and an average of 300 cases of RTIs per GP during the intervention period, amounting to a total of 2100 cases per cluster. The variance inflation factor [81], used to correct the sample size, was therefore 179.

Based on these figures and applying an 80% power level and a 5% statistical significance level, we estimate an intervention sample size requirement of 31 peer CME groups and a corresponding number of control groups.

We will carry out post-test comparisons between the intervention and control group using cluster-adjusted chi-square and *t*-tests. Analysis of covariance may be used to adjust for imbalance of baseline levels between the intervention- and control-groups [82]. The data set will primarily be analysed according to the cluster-randomization, however, analyses at physician- and sub-groups of physicians will also be performed, based on individual patients' data.

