Both Norwegian [55] and Danish [56] studies show great variation in GPs' prescription patterns for RTIs, and demonstrate a lack of adherence to current guidelines [21]. The potential for improvements are important, because community-wide antibiotic resistance reduces the effectiveness of currently available drugs to combat bacterial pathogens, and increases the individual patient's risk of becoming infected with drug-resistant organisms [57-59]. Previous studies have shown benefit from targeted educational intervention strategies towards GPs. Coenen et al. [60] reported that an (inter)actively delivered tailored intervention implementing a guideline for acute cough in a GP setting was successful for optimizing antibiotic prescribing without affecting patients' symptom resolution. Munck et al. [61] reported that a tailored audit of Danish GPs' antibiotic prescriptions for RTIs through the *Audit Project Odense (APO)*, resulted in a reduction in prescribed antibiotics, and that the large share proportion of broad-spectrum antibiotics was shifted to penicillin. The intervention effect in this study was significant, even two years after the intervention [61].

Welschen et al. [62] conducted a randomized controlled trial aimed at reducing antibiotic prescription rates for RTIs in primary care. The intervention included; a) group education meetings with consensus procedures and communication skills training, monitoring, and feedback on prescribing behaviour for GPs; b) group education for GPs' assistants and for pharmacists; and c) education materials for patients. At baseline, antibiotic prescription rates for RTIs were almost similar in the intervention and the control groups (27% and 29% respectively). Following the intervention, the prescribing rate in the intervention group fell to 23%, whereas it increased to 37% in the control group (mean difference of change; – 12%). The intervention did not influence patients' satisfaction or hospital referral rates [62].

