### Objectives

The primary objective of this trial is to evaluate the effects of a tailored intervention towards Norwegian GPs for a more rational approach to antibiotic prescriptions for RTIs. Our hypothesis is that an educational intervention program carried out during a 6-month period will be effective in improving prescribing patterns by reducing the total number of antibiotic prescriptions, as well as reducing the relative amount of broad-spectrum antibiotics, with special emphasis on macrolides. Degree of improvement will be measured by prevalence of specific antibiotic prescriptions and the combination of particular antibiotic prescriptions and selected diagnostic codes, according to the International Classification of Primary Care (ICPC-2) [76]. Secondary objectives are to estimate the agreement between prescribed and actually dispensed drugs, the latter based on dispensed drugs recorded in the Norwegian Prescription Database (NorPD), a national registry including data for all prescription drugs issued at Norwegian pharmacies, established in 2004 [77]. We will also explore effect of "delayed prescriptions" on the antibiotic prescription patterns.

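### The 27% planning rate is labelled as inappropriate prescribing, but the protocol's own account of the Dutch source makes it the rate of all antibiotic prescribing for RTI, so from that source the 80% power is unsupported for the named endpoint

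*Protocol article*

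**What the plan says.** The section Sample size and statistics opens with the planning rate: "A prevalence of 27% of inappropriate prescriptions of antibiotics for RTIs in general practice settings were found in two previous studies". It names one Norwegian and one Dutch study and concludes that "we anticipate a baseline prevalence of inappropriate prescription of antibiotics for RTIs of 27% in the present study".

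The target effect is relative: "we will consider a reduction of inappropriate prescriptions for RTIs by one third to be clinically significant". With control prescribing assumed constant, this is converted to "a reduction from a baseline level of 27% to a post-intervention level of 18% or less (9% absolute reduction; 33% relative reduction". With an intra-cluster correlation of 0.085, 2100 RTI cases per peer group, 80% power and 5% significance, the section arrives at 31 groups per arm.

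The Background describes the same Dutch trial differently: "At baseline, antibiotic prescription rates for RTIs were almost similar in the intervention and the control groups (27% and 29% respectively". The sample size section also describes that trial's effect without the word inappropriate, as a "12% reduction (absolute value) of antibiotic prescription rates for RTIs found by" that trial.

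The hypothesis under Objectives is that the programme "will be effective in improving prescribing patterns by reducing the total number of antibiotic prescriptions", as well as lowering the relative use of broad-spectrum agents.

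**The concern.** Within one section, the Dutch trial supplies a base rate labelled as inappropriate prescribing and an effect labelled as all antibiotic prescribing. The Background supports only the second label. The Discussion also relies on an earlier study, cited by the Dutch trial's reference number, to call the one-third cut in inappropriate prescribing realistic, so the ambiguity reaches the effect size too.

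The label matters because the denominator is RTI cases. In any one population, inappropriate prescriptions are a subset of all prescriptions for those cases. If about 27% of RTI cases receive an antibiotic, the inappropriate share is below 27% of cases unless nearly every prescription is inappropriate. Because the effect is a fixed relative reduction, a lower base rate also shrinks the absolute difference to be detected. Either the power claim lacks a matching input, or the sample size section names an outcome that its cited figure does not measure.

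**Working it through.** **Inputs (Sample size and statistics).** Rates 27% and 18%; ICC 0.085; 7 GPs × 300 cases = 2100 cases per cluster; power 80%; significance 5%, taken as two-sided because sidedness is not stated. The recruitment aim of about 80 groups (Participants) gives about 40 per arm.

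**Step 1: reproduce the plan.** Variance inflation = 1 + (2100 − 1) × 0.085 = 179.4 (the plan gives 179). The two-proportion formula for 0.27 against 0.18 gives 337 per arm, or 358.6 with continuity correction. Clusters per arm = 358.6 × 179.4 / 2100 = 30.6, rounded up to 31. This matches, so the calculation is correct for the inputs it uses.

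**Step 2: what the Dutch figures measure.** Background: baseline antibiotic prescribing rates of 27% and 29%, moving to 23% and 37%. Change: (23 − 27) − (37 − 29) = −4 − 8 = −12 points. This is the 12-point effect quoted in the sample size section, where it is again described as prescribing rates. The 27% and the 12 points belong to one series, all antibiotic prescribing for RTI.

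**Step 3: sensitivity to the base rate.** The documents give no separate inappropriate rate, so the base rates other than 27% are assumptions; 20.25%, 18% and 13.5% are three quarters, two thirds and one half of 27%. For base rate p1 and p2 = (2/3) × p1:

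- effective n per arm = k × 2100 / 179.4, which is 362.8 for k = 31 and 468.2 for k = 40
- power = Φ( (p1 − p2) / √{[p1(1 − p1) + p2(1 − p2)] / n} − 1.96 )

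Example, 18% to 12% with k = 31: the variance sum is 0.1476 + 0.1056 = 0.2532; the standard error is √(0.2532 / 362.8) = 0.0264; 0.06 / 0.0264 = 2.27; Φ(2.27 − 1.96) = 62%.

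| Base rate → target | Groups per arm needed (continuity-corrected) | Power, 31 per arm | Power, 40 per arm |
|---|---|---|---|
| 35% → 23.3% | 22 | 94% | 98% |
| 27% → 18% (plan) | 31 | 83% | 91% |
| 25% → 16.7% | 34 | 79% | 88% |
| 22% → 14.7% | 40 | 73% | 83% |
| 20.25% → 13.5% | 44 | 68% | 79% |
| 18% → 12% | 51 | 62% | 73% |
| 13.5% → 9% | 70 | 49% | 59% |

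The power columns carry no continuity correction, so their reference value is the 83% at 27%, not 80%. With the correction, power at 31 per arm is 80% at 27%, 76% at 25%, 58% at 18% and 44% at 13.5%. Uncorrected power with 31 groups drops below 80% at a base rate of about 25.3% (25.5% with a pooled null variance). With 40 groups the crossing is at just over 20%.

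**The case against.** The strongest reply is that none of this shows the trial to be short of power. Four parts of it carry weight.

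- **The Norwegian source.** It is also credited with 27% inappropriate prescribing and is described nowhere else in the article. It may support the label. This stands.
- **The subset argument.** A reader might infer that the inappropriate rate here must be below 27%. It does not follow, because a subset need only be smaller than its own total, not smaller than a Dutch trial's total. If 37% of cases here received an antibiotic (the Dutch control arm at follow-up), an inappropriate share of 73% would give 0.37 × 0.73 = 27%. The Norwegian rates in the Background are higher still, though they concern children and selected diagnoses. This stands, and it means the error could run in either direction.
- **The effect scale.** If 9 points absolute were kept, power with 31 groups would be about 95% at a base rate of 18% and 99% at 13.5%. The arithmetic is right, but the plan defines clinical significance as one third and derives the 9 points from it; 9 points from 18% would be a cut of one half. This part has little force.
- **The endpoint.** The section Outcome measures speaks of changes in prescription patterns and refers to a table that is not shown. If the powered endpoint is any antibiotic per RTI case, 27% is the right kind of input. This stands, but the sample size section would then name the wrong outcome.

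**Conclusion.** The point holds as a mislabelled planning input, not as an arithmetic error. The protocol describes the Dutch 27% in two incompatible ways and attaches 80% power to the reading that its own Background does not support. For inappropriate prescribing, 27% would be right only if nearly all prescriptions are inappropriate, if total prescribing in this population exceeds 27%, or if the undescribed Norwegian source bears it out.

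A reader might go further and conclude that the 80% power fails. The documents do not support that, because the trial's inappropriate rate is unknown. They support a conditional statement: with a one-third relative reduction, ICC 0.085 and 2100 cases per cluster, 31 groups per arm fall below 80% power if the rate is under about 25%, and exceed it if the rate is higher. The recruitment aim of about 40 per arm would absorb a rate down to just over 20%, but not 18% (73%) or 13.5% (59%). The point is of moderate weight: the stated power depends on it, and it is cheap to correct.

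**What to change.** State in Sample size and statistics which endpoint is powered, per RTI case, and give a base rate that measures it. There are two ways to do this.

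1. **Power on any antibiotic.** Attach the 27% to 18% calculation to the proportion of RTI cases given any antibiotic. This is what the Dutch figure measures, and it fits the first part of the hypothesis under Objectives. Reword the section accordingly; 31 groups per arm is unchanged. The one-third criterion must then be justified for total prescribing, because it is a different clinical target. For example, if half of prescriptions were inappropriate and the rest did not change, a fall from 27% to 18% would require inappropriate prescribing to fall from 13.5% to 4.5%, a cut of two thirds. The Dutch intervention arm itself fell by only 4 points, while the plan assumes constant controls.
2. **Keep inappropriate prescribing.** Replace 27% with a matching rate, for example from the baseline data extraction, and report power over a range of base rates for 31 to 40 groups per arm.

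In either case, say what the Norwegian source measured. The cost is a rewritten paragraph and a short table, with no added groups. The downside is that the stated power for inappropriate prescribing may become less favourable.

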**Methods/Design:**

Approximately 80 peer continuing medical education (CME) groups in southern Norway will be recruited to a cluster randomized trial. Participating groups will be randomized either to an intervention- or a control group. A multifaceted intervention has been tailored, where key components are educational outreach visits to the CME-groups, work-shops, audit and feedback. Prescription Peer Academic Detailers (Rx-PADs), who are trained GPs, will conduct the educational outreach visits. During these visits, evidence-based recommendations of antibiotic prescriptions for RTIs will be presented and software will be handed out for installation in participants PCs, enabling collection of prescription data. These data will subsequently be linked to corresponding data from the Norwegian Prescription Database (NorPD). Individual feedback reports will be sent all participating GPs during and one year after the intervention. Main outcomes are baseline proportion of inappropriate antibiotic prescriptions for RTIs and change in prescription patterns compared to baseline one year after the initiation of the tailored pedagogic intervention.

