### Outcome measures

Primary outcome measures will be changes in prescription patterns after the tailored educational intervention in terms of prescriptions for antibiotics in out-patients with RTIs. The intervention will include the option of "delayed prescriptions". Following the intervention, prescription data will be collected one year after the first (baseline) gathering of prescription data. Change in prescription patterns in the intervention group will be compared with the non-intervention control group, and with a sample of Norwegian GPs not included in the current trial. The latter data will be provided by the NorPD. Outcome measures are summarized in Table 2.

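### The main test ignores the baseline year that is collected, and adjusts for it only optionally on observed imbalance; always adjusting would gain precision and fix the primary analysis

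*Protocol article*

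**What the plan says.** Under Sample size and statistics, the article states the main analysis: "We will carry out post-test comparisons between the intervention and control group using cluster-adjusted chi-square" and t-tests. The opening of Methods/Design agrees, since the main hypothesis is to be tested on outcomes at follow-up. The next sentence under Sample size and statistics gives the only role for baseline: "Analysis of covariance may be used to adjust for imbalance of baseline levels between the intervention- and control-groups". No rule says what counts as imbalance, when the covariance analysis replaces the other test, or which of the two carries the conclusion.

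Baseline data will exist. Methods/Design says that prescription data are gathered in both arms at baseline and one year later, and the Intervention section says that the extraction covers the preceding 12 months.

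The outcome is worded as change. Outcome measures says "Primary outcome measures will be changes in prescription patterns after the tailored educational intervention" and adds that change in the intervention group is compared with the control group. The Abstract likewise lists "change in prescription patterns compared to baseline one year after the initiation of the tailored pedagogic intervention" among the main outcomes.

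**The concern.** Two things are at stake.

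- **Precision.** With clusters this large, the uncertainty of the arm difference comes almost wholly from true differences between peer groups in the follow-up year. An unadjusted post-test comparison leaves all of that in the error term. Each group's own earlier prescribing is the natural variable to take some of it out, and it is already being collected.
- **Definition of the primary analysis.** In a randomised trial a covariate is best chosen in advance because it predicts the outcome, not because the arms happen to differ on it. Tying adjustment to observed imbalance, with no rule, leaves the 5% level unattached to one defined procedure. It also leaves an outcome worded as change without a stated analysis that uses the baseline.

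**Working it through.** **Inputs.** From Sample size and statistics: 27% against 18%, with the control rate assumed constant; 80% power; 5% significance (sidedness not stated); ICC 0.085; 7 doctors × 300 cases = 2100 cases per cluster; variance inflation factor 179; 31 groups per arm. From Participants: a recruitment aim of about 80 groups, so 40 per arm. Assumed: r, the cluster-level correlation between baseline and follow-up rates, shown for 0.3 to 0.8.

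**1. The plan's own figure.** Variance inflation factor (VIF) = 1 + (2100 − 1) × 0.085 = 179.4. The two-sided formula for two proportions with continuity correction gives n = 359 per arm without clustering. Then 359 × 179.4 / 2100 = 30.7, so 31. (Without the correction: n = 337, giving 28.8, so 29.) The stated 31 therefore reproduces for an unadjusted post-test comparison. It takes no credit for baseline data.

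**2. Where the variance lies.**
- Between clusters: 0.085 × 0.27 × 0.73 = 0.01675.
- Sampling within a cluster: (1 − 0.085) × 0.27 × 0.73 / 2100 = 0.00009.

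More cases per cluster would gain almost nothing. With the number of clusters fixed, precision can improve only by explaining the first component.

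**3. Gain from baseline adjustment at 40 per arm.** Unadjusted SE = √[(0.27 × 0.73 + 0.18 × 0.82) × 179.4 / 2100 / 40] = 0.0271. Adjustment multiplies the SE by √(1 − r²). The detectable difference is 2.80 × SE, and power is Φ(difference/SE − 1.96). For a 6-point difference (27% against 21%) the unadjusted SE is 0.0278.

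| Analysis | Variance factor 1 − r² | Detectable difference, 80% power (points) | Power for 9 points | Power for 6 points |
|---|---|---|---|---|
| Unadjusted | 1 | 7.6 | 91% | 58% |
| r = 0.3 | 0.91 | 7.2 | 94% | 62% |
| r = 0.5 | 0.75 | 6.6 | 97% | 70% |
| r = 0.7 | 0.51 | 5.4 | >99% | 85% |
| r = 0.8 | 0.36 | 4.6 | >99% | 95% |

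The plan does not target 6 points. The column shows what happens if the effect is smaller than hoped. The article itself cites a 3% reduction in one earlier trial and concedes in its Discussion that a reduction of one third may look optimistic.

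**4. Why covariance analysis and not change scores.** Testing the change directly multiplies the unadjusted variance by 2(1 − r): 1.4 at r = 0.3, 1.0 at 0.5, 0.6 at 0.7 and 0.4 at 0.8. The corresponding factors for covariance analysis are 0.91, 0.75, 0.51 and 0.36, lower at every r shown.

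**5. Type I error of an open choice.** Simulation under the null with normal cluster-level data, 40 clusters per arm and 20,000 trials for each r from 0.3 to 0.8, at nominal 5%:
- always the t-test, or always covariance analysis: about 5%;
- covariance analysis only if the baseline difference has p < 0.10, otherwise the t-test: 4.7% at r = 0.3, falling to 2.3% at r = 0.8;
- the smaller of the two p-values: 6.5% at r = 0.3, rising to about 8.6% at r = 0.8.

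**The case against.** The strongest reply is that the default test is valid and the design adequate. The 31 groups per arm are right for the test as planned, and 40 per arm give about 91% power for the 9-point target. That stands: a reader who looks only at the 6-point figures might infer an underpowered trial, and the documents do not support that.

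Three further points also stand:

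- **Stability is not shown.** Between-cluster variance is 99.5% of the total (0.01675 of 0.01684), and a reader might take that share as stable over time. The ICC describes a single period. The between-cluster part includes true year-to-year change, so r has to be assumed. At r = 0.3 the gain is small.
- **Inflated type I error is not what the text describes.** An imbalance trigger gives an error rate below 5%. Inflation needs the analyst to take the better of two results. The article does not propose this; it only fails to exclude it.
- **Change versus level is not a validity problem.** Under randomisation, the follow-up difference, the difference in change and the covariance-adjusted difference all estimate the same effect in expectation. The mismatch between outcome and test concerns wording and precision.

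The last reply is that an analysis plan not shown may settle when covariance analysis applies. This is less persuasive. The article does not leave the test open: it names the unadjusted comparison and gives observed imbalance as the reason to adjust. Both are stated choices, and a better one is available from data already in hand.

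**Conclusion.** The point holds as one of efficiency and of an unfixed primary analysis. The article makes an unadjusted post-test comparison the main test and leaves baseline adjustment optional, although the baseline is collected in both arms and the outcome is worded as change. At 40 groups per arm, always adjusting would lower the detectable difference from 7.6 points to between 7.2 (r = 0.3) and 4.6 (r = 0.8). Power at the planned 9 points is already about 91% and would rise to between 94% and more than 99%. The loss matters most for a smaller effect: at 6 points, 58% unadjusted against 62% to 95% adjusted. Adjusting only after observed imbalance gives a conservative procedure, with about 2% to 5% type I error. A rate of about 6.5% to 8.6% arises only under selection of the more favourable test.

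These figures rest on the plan's ICC, cluster size and rates, on equal allocation of 80 groups, on a normal approximation at cluster level, and on an assumed r that is the same in both arms.

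**What to change.** State one primary analysis in Sample size and statistics: follow-up compared between arms, always adjusted for the cluster's own baseline rate, whether or not imbalance is seen. Either a cluster-level analysis of covariance or a mixed model with baseline as a covariate would serve. Keep the unadjusted chi-square and t-tests as sensitivity analyses, and remove the wording that ties adjustment to imbalance. Outcome measures can then say that the effect on change is estimated through this baseline-adjusted comparison.

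The cost is a sentence or two of text and one degree of freedom. No new data are needed. The sample size can stay as it is, since it is sufficient without the adjustment.
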